### Measures

Gender was, in a conventional way, assessed as biological sex as “woman” or “man.”

#### Primary Outcome Measures

Participants fill out a set of questionnaires regarding their weekly levels of autonomy-connectedness and ED symptoms.

To assess ED symptoms, the EDE-QS [36] is used. The EDE-QS is a brief, reliable, and valid measure of ED symptom severity. It consists of 12 items and was developed for routine, including session-by-session and outcome assessment, and it performs similarly to the Eating Disorder Examination Questionnaire (EDE-Q), which lends itself to the use of sessional outcome monitoring in treatment and research [37].

To assess weekly autonomy-connectedness levels, the Autonomy-Connectedness Scale (ACS-30) [38] was amended to allow for measuring short-term changes as the ACS-30-ST. The ACS-30-ST instruction asks about participants’ experiences during the past week (instead of “usually,” as in the original ACS-30). Existing questions have been rephrased where timing is concerned (eg, “I often long for…” has been changed to “In the past week I have longed for…”). The ACS-30-ST has been reviewed by a convenience sample to assess acceptability and feasibility, after which a few changes were made to questions that were hard to answer on a weekly basis (eg, “When making important decisions about my life, I leave other peoples’ opinions and wishes out of consideration” was changed to “When making decisions I leave other peoples’ opinions and wishes out of consideration.”) This process was repeated until the questionnaire was easy to use. Psychometric properties of the ACS-30-ST will be evaluated over the course of this study.

#### Secondary Outcome Measures

Every 3 months, participants fill out a longer set of questionnaires regarding their long-term autonomy-connectedness, ED pathology, depression, anxiety, self-esteem, and quality of life.

To assess autonomy-connectedness, the original ACS-30 is used [38]. This 30-item scale includes 3 subscales, self-awareness, sensitivity to others, and capacity for managing new situations. Items are rated on a 5-point Likert scale ranging from 1 (“disagree”) to 5 (“agree”). The reliability and validity are reported to be good [33].

To assess ED pathology, the EDE-Q is used [37]. This 22-item scale has been widely used to assess the frequency of disordered eating attitudes and behaviors, including restrictive eating, binge eating, and compensatory behaviors, occurring over the last 28 days. Items are scored on a 7-point scale ranging from 0 (no days or not at all) to 6 (every day or markedly). The scale includes 4 subscales: restraint (dietary restriction and attempts to limit food intake), eating concerns (preoccupation with eating and eating-related distress), shape concerns (concerns about body shape), and weight concerns (concerns about body weight). Internal consistency and 2-week test-retest reliability were excellent [37], and the global score showed strong discriminative validity in distinguishing individuals with an ED from those without [39].

To assess comorbid psychological symptoms, the depression and anxiety subscales of the Symptom Checklist-90 (SCL-90) are used [40]. The SCL-90 is a widely used measure of psychological distress with established reliability and validity in clinical and nonclinical populations [41].

To assess self-esteem, the Rosenberg Self-Esteem Scale (RSES) is used [42]. The RSES consists of 10 items and assesses global self-esteem. All items, containing positive and negative statements about the self, are rated on a 4-point Likert scale ranging from “strongly agree” to “strongly disagree.” The reliability and validity of the RSES are reported to be good [42].

To assess quality of life, the World Health Organization Quality of Life–Brief Version (WHOQOL-BREF) is used [43], which consists of 26 items, including 4 quality of life domains: physical health, psychological health, social relationships, and environment. Additionally, 2 items examine general quality of life. All items are rated on a 5-point Likert scale with 0 meaning “not at all,” “never,” “very poor,” or “very dissatisfied,” and 4 meaning “completely,” “always,” “very good,” or “very satisfied.” Psychometric properties have been studied in psychiatric outpatients and are reported to be good [44].

After treatment, an interview will be conducted to examine participants’ experiences with autonomy-enhancing therapy. The interview guide can be found in Multimedia Appendix 1.

### Analyses

Sample size and statistical power were approximated using G*Power (version 3.1.9.4). To detect a medium effect size (*f*^2^=0.15) in a regression with 7 predictors, 89 independent observations are needed for a power of 0.95 at α=.05. For the SCED analysis, with an intraclass correlation coefficient of 0.2, each participant’s 20 observations yield 4.17 independent observations [45], necessitating at least 22 participants. To ensure robustness, we aim for 30 participants (125 independent observations), achieving a power of 0.99. Considering a 20% dropout rate, we plan to recruit 36 participants. For the RM analysis, assuming 3 observations per participant, we obtain 30×2.14=64 independent observations, resulting in a power of 0.67 to detect a medium effect size (using α=.01).

Differences between individuals in their SCED data will be examined using visual analyses, presenting separate plots for all participants’ measures [46]. Visual analysis will evaluate changes in level, trend, variability, immediacy of effect, overlap between phases, and consistency across participants. Interview data will be used descriptively to better understand participants’ experiences of the intervention and their interpretation of change. The interview data will be reviewed and summarized to identify recurring experiences, perceived benefits and challenges, and considerations relevant to feasibility and future implementation.

The SCED data will be analyzed using a mixed model with 2 treatment periods, incorporating 2 dummy variables (treatment period 1 and treatment period 2, with baseline as the reference). A linear effect of time, centered within each period, represents the average change across periods. A random intercept and an autoregressive error structure will model the covariance structure. The primary hypothesis of the average decrease in ED symptoms is tested with 1 dummy for treatment period (1=treatment period 1 or 2, 0=baseline). This hypothesis will be tested for autonomy-connectedness.

The RM data for all outcome variables will be analyzed using mixed models. Measurement will be modeled with 3 dummy variables (after treatment period 1, after treatment period 2, and after 3 months, all with baseline as the reference category), and an unstructured covariance matrix will model the random effects. The analyses will focus on the effect of dummy “post,” testing the hypothesis that scores improve compared with baseline. Mediation by autonomy-connectedness will be tested in two steps: (1) adding autonomy-connectedness to the model and (2) conducting a dependent-samples *t* test (1-tailed) comparing autonomy-connectedness after treatment and at the 3-month follow-up with baseline. Mediation will be concluded if (1) autonomy-connectedness affects the outcome variable in the mixed model analysis and (2) autonomy-connectedness improves over time in the *t* test, indicating a joint-significance test of mediation [47].

All analyses will control for ED diagnosis (dummy AN, with BN as the reference category). We will explore whether the development over time of ED, autonomy-connectedness, and the other outcome variables differ between the two EDs.

Hypotheses on change will be tested 1-tailed, with a significance level of .05 for the multiple baseline data and .01 for the RM data to correct for multiple testing. Missing values on the outcome variable do not affect mixed model analyses [45], whereas participants with missing autonomy-connectedness values will be excluded from the mediation analyses.

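### The printed power figures (0.95, 0.99, 0.67) are not those of the planned one-tailed, within-person tests; the sample size can stay, but the figures should be restated

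*Protocol article*

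**What the plan says.** All power figures are in the protocol article, Methods, Analyses, which describes them as approximated with G*Power.

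- Effect and model: "To detect a medium effect size (*f*^2^=0.15) in a regression with 7 predictors".
- Requirement: "89 independent observations are needed for a power of 0.95 at α=.05".
- Weekly data (single-case design): "with an intraclass correlation coefficient of 0.2", a participant's "20 observations yield 4.17 independent observations", "necessitating at least 22 participants". Then: "we aim for 30 participants (125 independent observations), achieving a power of 0.99".
- 3-monthly data (repeated measures, RM), at alpha .01: "we obtain 30×2.14=64 independent observations, resulting in a power of 0.67 to detect a medium effect size".

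The tests themselves are described in the same section and under Design. The primary weekly test is a single dummy for treatment against baseline, in a model with a random intercept and autoregressive errors. The RM test is the post dummy against baseline, with the other measurement dummies in the model. Design states that participants act as their own controls. On sidedness: "Hypotheses on change will be tested 1-tailed, with a significance level of .05 for the multiple baseline data", and .01 for the RM data.

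**The concern.** A stated power should be the power of the test that will be run. Three features suggest that these figures are not.

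1. The deflator 1+(m−1)·ICC is the variance inflation for an average over people or for a predictor that differs between people. For a contrast within a person, the random intercept drops out. A higher ICC then raises power, whereas the plan's formula lowers it. The formula also has no place for the planned autoregressive error, or for variation between patients in how they respond.
2. The figures appear to be two-tailed although the hypotheses on change are one-tailed.
3. The medium label belongs to f² as a regression convention. For a phase or wave dummy, the same value is a large mean shift, in patients whom the Participants section describes as already in behavioral remission.

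At stake is what a reader may conclude from the power statement, above all for the RM analyses, which carry every secondary outcome.

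**Working it through.** **1. Reproducing the plan's figures.** Inputs from Analyses: f²=0.15, 7 predictors, ICC 0.2, m=20 or 3 observations.

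- Effective observations per person, m/(1+(m−1)·ICC): 20/(1+19×0.2)=20/4.8=4.17; 3/(1+2×0.2)=3/1.4=2.14.
- 89/4.17=21.4, hence 22 participants; 30×4.17=125; 30×2.14=64.
- Power of one regression coefficient: noncentral t with noncentrality √(f²N) and N−8 degrees of freedom.

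| N, alpha | Stated | Two-tailed | One-tailed |
|---|---|---|---|
| 89, .05 | 0.95 | 0.951 | 0.976 |
| 125, .05 | 0.99 | 0.990 | 0.996 |
| 64, .01 | 0.67 | 0.667 | 0.757 |

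One-tailed, 74 observations already give 0.95. An overall F test of all 7 predictors gives 0.72 at N=89, so it is not the source. The arithmetic is right on its own inputs, and the calculation is the two-tailed one.

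**2. What f²=0.15 means as a shift.** For a phase dummy with baseline share p, f²=p(1−p)d², with d in residual SDs.

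- 5 of 20 points at baseline: d=√(0.15/(0.25×0.75))=0.89.
- 6.5 of 20: d=√(0.15/(0.325×0.675))=0.83.
- 8 of 20: d=√(0.15/(0.40×0.60))=0.79.

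For RM with the 3 waves used in the plan's calculation, the post dummy has variance 1/6 once the other wave dummy is in the model: d=√(0.15×6)=0.95.

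**3. Direction of the design-effect error.** Take a total SD of 1, p=0.325, ICC 0.2 and independent residuals. Per-person variance of the treatment-minus-baseline contrast:

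- plan's formula: 1/(4.17×0.325×0.675)=1.09;
- within-person: (1−0.2)×(1/6.5+1/13.5)=0.18.

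The ratio is 4.8/0.8=6. At n=30 the standard errors are √(1.09/30)=0.19 and √(0.18/30)=0.08. Generalised least squares (GLS) for the planned model gives 0.079 with no autocorrelation, 0.122 with AR(1)=0.7, and 0.153 with AR(1)=0.7 plus a between-person effect SD of 0.5. All are below 0.19, so the plan's formula is conservative over this range.

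**4. Weekly (single-case) power.** GLS with random intercept, AR(1) error, period-centred time, a diagnosis dummy, and baselines of 5, 6, 7 or 8 out of 20 points; one-tailed .05, reference t with n−1 degrees of freedom. Assumed ranges: ICC 0.2 to 0.5, AR(1) 0 to 0.7. The last column adds an assumed between-person effect SD of 0.5.

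| n | Shift (SD) | Uniform response | With effect SD 0.5 |
|---|---|---|---|
| 30 | 0.8 | >0.99 | >0.99 |
| 30 | 0.5 | 0.99 or more | 0.94 or more |
| 30 | 0.3 | 0.77 to >0.99 | 0.61 to 0.84 |
| 22 | 0.5 | 0.96 or more | 0.86 or more |
| 22 | 0.3 | 0.65 to 0.99 | 0.49 to 0.73 |

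**5. RM power.** Paired contrast, n=30, one-tailed .01, standardised difference d/√(2(1−r)), 29 degrees of freedom. The within-person correlation r is assumed. Example: d=0.5, r=0.5 gives 0.5/√1=0.5, noncentrality 0.5×√30=2.74, power 0.61.

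| Shift (SD) | r=0.2 | r=0.5 | r=0.7 |
|---|---|---|---|
| 0.5 | 0.40 | 0.61 | 0.85 |
| 0.8 | 0.84 | 0.97 | >0.99 |
| 0.95 | 0.94 | >0.99 | >0.99 |

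**The case against.** The strongest defence is that the errors are on the safe side. The plan calls its power approximate, every figure reproduces, and 0.15 is the conventional medium f² with its value disclosed. For the specified effect, both the design effect and the two-tailed calculation understate power. In the weekly data, even a 0.5 SD shift has power of about 0.99 or more at 30 participants with uniform response, so the printed 0.99 is not misleading there. The plan also already discloses RM power below 0.8. With 18 participants reported as completed, no test or decision would change.

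Most of this stands. A reader might infer that the trial is underpowered, or that a null weekly result would be wrongly taken as strong evidence against a 0.5 SD effect. The documents do not support either inference. Nor can a loss of power be shown by putting a larger ICC or a smaller shift into the plan's own effective numbers, because that relies on the formula in dispute and gets the direction of the ICC wrong.

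The defence does not rescue the figures as descriptions of the tests. The clash over sidedness is internal to the article. The RM value of 0.67 is too low for the effect that f²=0.15 implies. For a 0.5 SD change it is correct only at some correlation between 0.5 and 0.7, which the plan does not state.

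**Conclusion.** The point holds as a misstated property of the design, not as a shortfall in sample size. The stated powers come from a between-person, two-tailed calculation, while the planned tests are within-person and one-tailed. The practical gap is small for the weekly data at 0.5 SD and above. It becomes material only near 0.3 SD, a size for which the plan claims no power. It is clearest for RM: 0.67 is the plan's two-tailed value, 0.76 its one-tailed equivalent, and the paired test gives 0.40 to 0.85 for 0.5 SD and 0.94 or more for 0.95 SD.

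Steps 1 and 2 need only the plan's inputs. The power ranges in steps 4 and 5 rest on assumed ICC, autocorrelation, within-person correlation and effect spread, because the article gives only an ICC of 0.2. They also take the plan's 20 weekly observations per person, although baselines of 5 to 8 weeks and 12 to 24 weeks of therapy allow 17 to 32.

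**What to change.** Keep the sample size and rewrite the power paragraph for the tests that will be run.

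- Weekly data: simulate the planned model or use GLS (random intercept, autoregressive error, staggered baselines), one-tailed .05, with and without between-person spread in the phase effect.
- RM data: paired post-versus-baseline contrast, one-tailed .01.
- State effects as SD shifts (0.3, 0.5, 0.8) rather than f², and show power over stated ranges of ICC, autocorrelation and effect spread. Baseline weeks of the completed participants could supply the variance parameters without looking at treatment effects.
- If the existing figures are kept for the record, label them as a two-tailed approximation that is conservative for f²=0.15, and give the SD shift to which that corresponds.

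The cost is a short calculation and one paragraph. The downside is that RM power for a 0.5 SD change may look less favorable than the present statement.

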## Results

Data collection started in March 2024. As of May 2026, 18 participants have completed the study, and 6 have been enrolled. An additional 7 participants have been recruited, whose participation will depend on their individual treatment paths. Data collection is projected to finish in February 2027; results are expected to be published in the second half of 2027.

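### The allowance for 20% dropout is computed as 30 × 1.2 = 36; at that rate 36 recruits leave about 29 participants, not the 30 at which both powers are stated

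*Protocol article*

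**What the plan says.** All the planning figures stand in the first paragraph of Analyses in the protocol article.

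- The calculation starts from a regression: "To detect a medium effect size (*f*^2^=0.15) in a regression with 7 predictors", for which "89 independent observations are needed for a power of 0.95 at α=.05".
- For the single-case experimental design (SCED), "with an intraclass correlation coefficient of 0.2", 20 weekly observations count as 4.17 independent ones, "necessitating at least 22 participants".
- A margin is then added: "we aim for 30 participants (125 independent observations), achieving a power of 0.99".
- The dropout allowance follows: "Considering a 20% dropout rate, we plan to recruit 36 participants".
- For the repeated measures (RM) analysis, 30 × 2.14 = 64 independent observations are said to give a power of 0.67 at α = .01.

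The last paragraph of Analyses specifies one-tailed tests of change, at .05 for the weekly data and .01 for the RM data. The Participants section gives a planned sample of 22 to 30. The Results section reports the status so far: "18 participants have completed the study, and 6 have been enrolled". It adds: "An additional 7 participants have been recruited, whose participation will depend on their individual treatment paths".

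**The concern.** The target of 30, the dropout rate of 20% and the recruitment figure of 36 do not fit together. Adding 20% to the target is not the same as allowing for a 20% loss from those recruited. At the plan's own rate, 36 recruits fall short of 30, and 30 is the number on which both powers rest. The RM power matters more. It is already only 0.67, and the RM analysis carries the secondary outcomes and the mediation test.

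**Working it through.** **Inputs, all from Analyses:** target 30; dropout 20%; recruitment 36; f² = 0.15; 7 predictors; ICC 0.2; 20 weekly and 3 RM observations per participant; α = .05 (SCED) and .01 (RM).

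**1. Reproducing the stated recruitment.** 30 × (1 + 0.20) = 36, an exact match. The allowance for a loss from those recruited is 30/(1 − 0.20) = 37.5, so 38. In the other direction, 36 × (1 − 0.20) = 28.8, which is 28 whole participants or 29 to the nearest. A recruitment of 36 retains 30 only if dropout is 6/36 = 16.7%.

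**2. Reproducing the effective observations.** With m observations per participant, m/(1 + (m − 1) × ICC) gives 20/(1 + 19 × 0.2) = 4.17 and 3/(1 + 2 × 0.2) = 2.14. Then 89/4.17 = 21.4, so 22 participants; 30 × 4.17 = 125; 30 × 2.14 = 64. All match the article.

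**3. Reproducing the powers.** The test is of one regression coefficient, using the noncentral t distribution with n − 7 − 1 degrees of freedom and noncentrality √(f² × n), where n is the number of effective observations. Two-sided, a power of 0.95 at .05 needs n = 89, as stated. A one-sided test would need 74 and an omnibus F test 153. Two-sided power is 0.990 at n = 125 (α = .05) and 0.667 at n = 64 (α = .01), again as stated. The printed figures are therefore two-sided.

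**4. Powers at the number retained** (effective observations rounded down):

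| Retained | SCED n | SCED two-sided .05 | SCED one-sided .05 | RM n | RM two-sided .01 | RM one-sided .01 |
|---|---|---|---|---|---|---|
| 30 | 125 | 0.990 | 0.996 | 64 | 0.667 | 0.757 |
| 29 | 120 | 0.988 | 0.995 | 62 | 0.648 | 0.741 |
| 28 | 116 | 0.985 | 0.994 | 60 | 0.629 | 0.724 |

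Moving from 30 to 28 or 29 costs 0.2 to 0.5 percentage points of SCED power and about 2 to 4 points of RM power on the two-sided calculation. On the one-sided calculation the RM cost is 1.6 to 3.3 points, but from a starting value of 0.757.

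**The case against.** The case for leaving the text alone has four parts.

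- **The gap is two recruits.** The number the article derives as necessary is 22; 30 is a margin, and 28 to 29 lies within the planned 22 to 30. This stands for the SCED analysis, where power barely moves. It does not cover the RM power, which is quoted only at 30.
- **The tests are one-tailed.** For the one-tailed .01 test, RM power at 28 to 29 is 0.72 to 0.74, above the printed 0.67. This stands. It means that 0.67 is not too optimistic for the specified test, and that the calculation and the test differ in sidedness.
- **Participants who leave still contribute.** The mixed models keep their observed outcomes, so counting only those retained understates the information. This stands for the outcome models. It does not help the mediation analyses, from which participants with missing autonomy-connectedness values are excluded.
- **The recruitment figure is only a plan.** True, but the three numbers stand next to each other and disagree.

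A stronger reading is tempting. The Results counts sum to 18 + 6 + 7 = 31, and a reader might infer that recruitment ends there, 5 short of 36, or that 24 to 31 will complete. The article does not support this. The counts are an interim status, with data collection open until February 2027 and no statement that recruitment has closed. Earlier dropouts are not reported, so 31 (18 who have completed plus 13 who have not) cannot be set against 36 recruited before any loss. A lower end of 24 = 18 + 6 would assume that none of the 6 enrolled is lost. The status date itself differs: the Abstract gives September 2026 and the Results section May 2026 for the same counts. That weakens any inference about the time left to recruit.

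**Conclusion.** The dropout allowance is wrong by a small amount. At 20% dropout, 36 recruits leave 28.8 participants, and 38 would be needed to retain 30. By the plan's own two-sided method, SCED power stays at about 0.99 and RM power becomes 0.63 to 0.65 instead of 0.67. Under the one-tailed .01 test that the article specifies, RM power is 0.72 to 0.74. Whether the printed RM figure is too high or too low therefore depends on the sidedness, which the power statement does not give. These figures take over the article's effect size, ICC, number of predictors and dropout rate, and count only retained participants. Because partial outcome data are kept, the loss of information in the mixed models is at most this size. The SCED analysis of the primary outcomes is not threatened, and nothing here shows that recruitment is failing.

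**What to change.** Choose one of two corrections in Analyses:

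1. Change the recruitment figure to 38, as 30/0.8 rounded up, to retain 30.
2. Keep 36, state that about 29 are expected to be retained at 20% dropout, and give the powers at that number: SCED about 0.99, and RM about 0.63 to 0.65 two-sided or 0.72 to 0.74 one-tailed (28 to 29 retained).

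In either case, say which sidedness the powers assume, so that they can be matched to the one-tailed tests. The second option costs a sentence or two, with no extra enrolment and no change to the analysis. The first implies two more recruits.

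### The weekly SCED model allows no between-person variation in the phase effect; if responses differ between participants, the standard error of the average effect is too small and the one-tailed 5% test too liberal

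*Protocol article*

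**What the plan says.** The Analyses section of the protocol article fixes the covariance model for the weekly data: "A random intercept and an autoregressive error structure will model the covariance structure". The test is on a single fixed coefficient: "The primary hypothesis of the average decrease in ED symptoms is tested with 1 dummy for treatment period", and the same test is planned for autonomy-connectedness. On error rate: "Hypotheses on change will be tested 1-tailed, with a significance level of .05 for the multiple baseline data".

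Variation between people in the weekly data is assigned to plots: "Differences between individuals in their SCED data will be examined using visual analyses". The section names no random phase effect, robust standard error or randomization test for these data.

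An unstructured covariance matrix does appear, at the end of the repeated-measures paragraph under Design and again under Analyses. Both places concern the 3-monthly data, so it does not cover the weekly model.

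**The concern.** The primary question is the average change across participants, each contributing about 17 weekly scores (5 baseline plus 12 treatment) to 32 (8 plus 24). A random intercept shifts a participant's baseline and treatment scores equally, so it cancels out of the phase contrast. It cannot represent one participant improving more than another. The autoregressive term covers week-to-week dependence and absorbs only part of such a difference.

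If individual phase effects have SD τ, the variance of their average over N people contains a term of about τ²/N. Extra weeks per person do not reduce that term, but under the stated model extra weeks keep shrinking the reported standard error. The p value and interval for both primary outcomes would then be too favorable. In a one-tailed test in a study without a control arm, that error favors the therapy.

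**Working it through.** **1. The plan's own figures.** The article has "in a regression with 7 predictors, 89 independent observations are needed for a power of 0.95 at α=.05", "with an intraclass correlation coefficient of 0.2", and "20 observations yield 4.17 independent observations".

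- Effective observations per person: m/(1+(m−1)×ICC) = 20/(1+19×0.2) = 20/4.8 = 4.17.
- Participants needed: 89/4.17 = 21.4, hence 22. With 30 participants: 30×4.17 = 125.
- Noncentral t power for one coefficient (f² = 0.15, 7 predictors, two-sided 5%): 0.951 at 89 observations and 0.990 at 125.

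All reproduce. The ICC is the only between-person term, so the planning also has no allowance for varying phase effects.

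**2. Inputs for the check.**

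- From the article: 30 participants, baselines of 5 to 8 weeks, treatment of 12 to 24 weeks, ICC 0.2, random intercept plus autoregressive error, one fixed phase dummy, time centered within period, diagnosis as covariate, one-tailed 5%.
- Assumed: total baseline variance 1 (so τ is in baseline SD units), first-order autoregression, half the participants treated for 12 weeks and half for 24, τ from 0 to 0.6, autocorrelation 0.3 or 0.5. The article gives no value for τ or the autocorrelation.

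**3. Method.** The stated model was fitted by expected likelihood to data whose true covariance includes a random phase effect of SD τ. Its model-based standard error was compared with the true (sandwich) standard error of the same estimate. Actual one-sided level = Φ(−1.645 × reported SE / true SE).

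| Autocorrelation | τ | Reported SE | True SE | SE too small by | Actual level |
|---|---|---|---|---|---|
| 0.3 | 0 | 0.095 | 0.095 | 0% | 5.0% |
| 0.3 | 0.2 | 0.096 | 0.102 | 6% | 6.1% |
| 0.3 | 0.3 | 0.097 | 0.110 | 12% | 7.3% |
| 0.3 | 0.4 | 0.099 | 0.120 | 18% | 8.8% |
| 0.3 | 0.6 | 0.104 | 0.146 | 29% | 12.1% |
| 0.5 | 0 | 0.107 | 0.107 | 0% | 5.0% |
| 0.5 | 0.2 | 0.108 | 0.113 | 5% | 5.8% |
| 0.5 | 0.3 | 0.109 | 0.120 | 9% | 6.8% |
| 0.5 | 0.4 | 0.111 | 0.130 | 15% | 8.0% |
| 0.5 | 0.6 | 0.115 | 0.154 | 25% | 10.9% |

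**4. Hand check.** True variance ≈ (SE at τ = 0)² + τ²/N. For τ = 0.4 and autocorrelation 0.3: 0.095² + 0.16/30 = 0.00903 + 0.00533 = 0.01436, whose root is 0.120. The level is Φ(−1.645 × 0.099/0.120) = Φ(−1.36), about 8.7% with these rounded values. At τ = 0.6 the fitted autocorrelation rises from 0.30 to 0.36, so the autoregressive term takes up some of the extra variance but far from all of it.

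**5. Simulation check.** With 3,000 REML fits per setting (Monte Carlo SE about 0.4 to 0.6 points), levels for τ = 0, 0.2, 0.3, 0.4 and 0.6 were:

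- autocorrelation 0.3: 4.1%, 6.6%, 7.0%, 9.8% and 13.0%;
- autocorrelation 0.5: 4.5%, 6.5%, 7.0%, 7.8% and 10.7%.

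A paired test on person-level means held 4.4% to 5.9% on the same data. A smaller run (600 fits) gave 8.7% at τ = 0.6 and autocorrelation 0.3. Its paired comparator was also low (2.0%), so the larger run is the better guide.

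**6. Wider assumptions.** With τ from 0.2 to 0.8, autocorrelation 0, 0.3 or 0.6, and all participants on 12 weeks, all on 24, or half each, the level runs from 5.6% to 19.7%.

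**The case against.** **The inflation is conditional.** If the therapy changes nobody and nothing else moves people differently between phases, τ is zero and the test is exact. This stands, and the point is worded accordingly.

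**The article does not say that phase effects vary.** A reader might infer from the individual plots and the check of consistency across participants that the plan expects differing responses, so that the test is shown to be too liberal. The text says only that differences will be examined. Patients also enter this phase in behavioral remission, which may limit the spread of symptom change. Nothing in the article supports a particular τ, so no single inflation figure can be given as fact. Equal effects are still a strong assumption when therapy lasts 12 to 24 weeks, two diagnoses are mixed and usual treatment continues alongside.

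**The p value is not the only evidence.** The design relies on replication across staggered baselines and on visual analysis, and the Discussion concedes limited generalizability. Read as a statement about these participants only, the reported standard error could be defended. But the stated objective is effectiveness in this phase of care, and the sample size is built on this regression test. That question needs an error term that includes variation between people.

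**A richer model may be hard to fit.** With 22 to 30 people and 5 to 8 baseline points each, the random-phase variance may be weakly identified. In a small simulation (150 to 300 runs, Monte Carlo error about 2 points) that model ran at about 6% to 7%. This argues for small-sample degrees of freedom and a fixed fallback, not for leaving the term out.

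**Conclusion.** The point holds in conditional form. The covariance model is stated outright, so this is a choice in the plan and not a detail left to another document. Whenever phase effects differ between participants, the reported standard error of the average effect is too small and the one-tailed 5% test too liberal. When they do not differ, the test keeps its level.

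Under the assumptions listed, a modest spread (0.2 to 0.3 baseline SD) takes the level to about 6% to 7%, and a larger one (0.4 to 0.6) to about 8% to 12%. The direction is sure given any spread; the size is not, because it rests on two quantities that the article does not give. Severity: should-fix.

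**What to change.** Before the final analysis, prespecify a participant-level random effect for the single treatment-phase dummy, added to the random intercept and autoregressive error. State whether Satterthwaite or Kenward-Roger degrees of freedom will be used. Name one fallback for a singular fit: the planned structure with small-sample cluster-robust (CR2) standard errors by participant. Do not add a random time slope that depends on convergence, because the primary model would then be chosen by the data.

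No change to design or data collection is needed. Collection is projected to run to February 2027, so there is time to record the change.

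The cost is a somewhat wider interval when responses differ (for example, a standard error of 0.120 instead of 0.099 at τ = 0.4 and autocorrelation 0.3), almost nothing when they do not (0.095 under both models), and possible convergence problems.
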